#### **Other Relevant Topics of Planned Data Analysis**

Data analysis will include additional exploratory objectives for which detailed statistical methods will be indicated in separated document - Statistical Analysis Plan. The following exploratory objectives will be under investigation:

1. To assess effectiveness of Betaserc® and the course of vestibular vertigo in post-treatment period in subgroups of patients with different underlying diagnosis according to ICD-10.
2. To describe concomitant medication for vestibular vertigo during program period according to underlying ICD-10 diagnosis.
3. To describe effectiveness Betaserc® and the course of vestibular vertigo in post-treatment period in the subgroups of sex (males and females) and countries (Russia and Ukraine).

Also, the number and percent of subjects experiencing serious adverse events (SAEs (including deaths) and adverse events leading to discontinuation of program drug will be

[figure not shown]

tabulated according to the primary MedDRA system organ class (SOC) and MedDRA preferred term.

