| Overall clinical response and clinical response as improvement of vestibular vertigo associated symptoms based on four-point scales  |                        | X                                                                                 | X                                                                                 |                                                                    |                                                           |
| SAE monitoring                                                                                                                       | X                      | X                                                                                 | X                                                                                 | X                                                                  |                                                           |

 This program does not include patients who required betahistine therapy, according to physician's decision, more than 60 days.

 Actual date of visit may be up to 7 days from the last betahistine dose, otherwise proceed to Visit 4.

[figure not shown]

 This coincides with Visit 2 in case patient had completed betahistine treatment period lasting 30 days or less. In case physician decides to continue betahistine therapy beyond 30 days, Visit 3 will be a separate visit from Visit 2.

 For patients whom physician decides to continue betahistine therapy beyond 60 days treatment course, no follow up will be done and end of observational treatment period will denote end of program.

 Includes sex, age, race (white, black, asian, other), weight and height

 Heart rate, blood pressure (systolic and diastolic)

 for more detailed information about Scale for Vestibular Vertigo Severity Level and Clinical Response Evaluation please see section 6.3, Figure 1 and Table 1.

 Four-point-scale, where 4 = excellent, 3 = good, 2 = fair, and 1 = poor.

 30 days after end of program treatment or early termination, a telephone call will be made to enquire about development of any SAE. If there is a positive feedback, relevant medical history and adverse event details will be collected.

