**Visit 2, up to 30th day from the first dose of Betaserc®:**

The following procedures will be performed:

- Register concomitant medication
- Evaluate patient's clinical conditions based on SVVSLCRE
- Register of the number of vertigo attacks for the previous month
- Assess overall clinical response and clinical response as improvement of vestibular vertigo associated symptoms based on four-point scale
- SAE monitoring

**Visit 3, up to 60th day from the first dose of Betaserc®, End of Observational Treatment Period / Early Termination:**

The following procedures will be performed:

- Register concomitant medication
- Evaluate patient's clinical conditions based on SVVSLCRE
- Register of the number of vertigo attacks for the previous month

[figure not shown]

- Assess overall clinical response and clinical response as improvement of vestibular vertigo associated symptoms based on four-point scale
- SAE monitoring

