## **8.2 Severity**

The physician will use the following definitions to rate the severity for any adverse event being collected as an endpoint/data point in the study and for all serious adverse events.

- |                  |                                                                                                                                       |
|------------------|---------------------------------------------------------------------------------------------------------------------------------------|
| Mild:     | The adverse event is transient and easily tolerated by the subject.                                                                   |
| Moderate: | The adverse event causes the subject discomfort and interrupts the subject's usual activities.                                        |
| Severe:   | The adverse event causes considerable interference with the subject's usual activities and may be incapacitating or life threatening. |

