## **8.4 Serious Adverse Event Collection Period**

Serious adverse events will be reported to Abbott from the time the physician obtains the patient's authorization to use and disclose information (or the patient's informed consent) until 30 days following the intake of the last dose of physician-prescribed treatment.

[figure not shown]

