### **Sample size considerations**

Based on evaluation of literature data that was published by Gananca et al. in *Acta Oto-Laryngologica*, 2009 [17], proportion of patients with Meniere's Disease achieved control of vertigo (clinical conditions levels 4 and 3) after 12 weeks of treatment with betahistine dihydrochloride tablets constituted 88%. Benecke et al. [18] found that overall efficacy of betahistine in routine clinical practice over 3 months therapy was excellent by 36.6% of 1753 patients with recorded data (n = 641) and good by 49.6% of patients (n = 870), total 86.2 %. The investigators' impression of the treatment was excellent for 38.6% of patients (n = 675 of 1747) and good for 50.5% of patients (n = 883), total 89.1%.

For this program, it is assumed that at least 80% of the total study sample will achieve clinical response after 60 days of therapy with betahistine dihydrochloride tablets. When the sample size without a consideration of dropout is 246, a normal approximation two-sided 95% confidence interval for a single proportion using normal distribution will extend 5.0% (i.e. half width of the 95% confidence interval) from the observed proportion for an expected proportion of 80% [19; 20]. Considering an approximate dropout rate about 20%, total study population (received at least one dose of betahistine dihydrochloride (Betaseron®) tablets and have at least one post-baseline assessment) will constitute 308 patients.

Overall, the best consideration for total number of enrolled patients with vestibular vertigo in the program has to amount 310.

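### The protocol plans a table of adverse events leading to discontinuation, but its collection procedures cover serious adverse events only

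*Protocol*

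**What the plan says.** **The planned output.** The last paragraph of Section 11.0, Other Relevant Topics of Planned Data Analysis, promises the number and percent of patients experiencing "serious adverse events (SAEs (including deaths) and adverse events leading to discontinuation of program drug will be" tabulated by MedDRA system organ class and preferred term.

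**The collection.**
- Table 2 has one safety row, for serious adverse event (SAE) monitoring, marked at Visits 1 to 4.
- In Section 7.5.2 the only safety item at Visits 1 to 4, including Visit 3/Early Termination, is "SAE monitoring". Visit 5 has none.
- Table 2 footnote 9 describes the post-treatment contact: "30 days after end of program treatment or early termination, a telephone call will be made to enquire about development of any SAE". Section 7.5 describes the same contact, also for SAEs.
- Section 8.4 sets a collection period for one class of event: "Serious adverse events will be reported to Abbott from the time the physician obtains the patient's authorization to use and disclose information" (or consent), up to 30 days after the last dose. Section 8.5 gives a reporting route for that class only.
- Table 2 and Section 7.5.2 register the date treatment started. Neither lists a reason for stopping.

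**Patients treated beyond day 60.** Footnote 4 of Table 2 says of them that "no follow up will be done and end of observational treatment period will denote end of program".

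**The concern.** The analysis section and the collection sections do not describe the same data. Adverse events leading to discontinuation stand beside SAEs as a category of their own. Had only serious events been meant, the second category would be a subset of the first and the wording would have said so. A site that carries out each listed activity would nonetheless have no instruction to record a non-serious event that made a patient stop.

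An analysis plan cannot repair this, because it cannot tabulate events that sites were never told to record. At stake is one stated safety output: its numerator would omit non-serious events, and a reader of the report could not tell whether none occurred or none were sought.

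**Working it through.** **Step 1. The plan's own figures.** The only denominators in the protocol come from the sample size paragraph, where "it is assumed that at least 80% of the total study sample will achieve clinical response after 60 days of therapy".
- n = 1.96² × 0.80 × 0.20 / 0.05² = 245.85, rounded up to 246 (agrees).
- 246 / (1 − 0.20) = 307.5, rounded up to 308 (agrees). Enrolment is set at 310.

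These figures reproduce and are not in dispute. 310 serves below only as a denominator.

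**Step 2. Planned table against each collection provision.**

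| Provision | Serious events | Non-serious events leading to stopping | Reason for stopping |
|---|---|---|---|
| Section 11.0 table | planned | planned | implied |
| Table 2 | Visits 1–4 | not listed | not listed |
| Section 7.5.2, Visits 1–4 | listed | not listed | not listed |
| Section 7.5.2, Visit 5 | not listed | not listed | not listed |
| 30-day contact (7.5, footnote 9) | asked | not asked | not asked |
| Sections 8.4 and 8.5 | period and route | neither | neither |

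The first row has no source for its second column.

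**Step 3. Possible size.** The documents give no rate of stopping for adverse events, so every rate here is an assumption.
- If 2% to 5% of patients stop for a non-serious event: 310 × 0.02 = 6.2 and 310 × 0.05 = 15.5, so about 6 to 16 patients. This is a ceiling for those rates, since it supposes that none is recorded by another route.
- Alternatively, let r be the rate of stopping for any adverse event and s the serious share. Expected stops are 310r, stops captured by SAE-only collection are 310rs, and the chance of no captured case is (1 − rs)^310. For r from 1% to 5%, 3.1 to 15.5 patients stop. For s from 0% to 20%, 0 to 3.1 are captured.
- At r = 2% and s = 10%: 6.2 stop, 0.62 are captured, and the chance of none is 0.998^310 = 0.54. At r = 5% and s = 20%: 15.5 stop, 3.1 are captured, and that chance is 0.99^310 = 0.04.
- A count of zero in 310 has a two-sided exact 95% upper limit of 1 − 0.025^(1/310) = 1.2%. That limit would not be valid for non-serious events if they were not asked about.

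**Step 4. Patients continuing past day 60.** Footnote 4 ends their participation at the end of the observational treatment period. Section 8.4 keeps SAE reporting open until 30 days after the last dose, which for them falls after that point. Footnote 9 requires a call 30 days after program treatment ends, and Section 7.5 times that contact from the last dose. The passages give these patients no single end date for SAE collection.

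**The case against.** The best reply is that the protocol does not forbid collecting other events. Section 8.2 asks for a severity rating of "any adverse event being collected as an endpoint/data point in the study and for all serious adverse events", which leaves room for non-serious events. Section 8.3 speaks of adverse events generally. Section 11.0 plans to present disposition, and the case report form is not shown, so a discontinuation page may exist. This stands to a degree: the gap is an activity that nobody is told to perform, and it does not prove that the data will be absent. But Section 8.2 names no such event, and neither do Sections 6.3 and 6.4, Table 2 or Section 7.5.2. A protocol should not depend on an unseen form for an output it promises.

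On footnote 4, the follow-up it rules out may be only Visits 4 and 5, and Section 7.1 and footnote 1 mean to leave out patients needing more than 60 days. That narrows the conflict to an uncertain end date in a group intended to be small or absent.

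A reader might go further in several ways that the documents do not support:
- That the table will be nearly empty and taken as evidence of good tolerability. No rate is given, the chance of an empty table swings widely with the assumptions, and the protocol has no tolerability objective.
- That intolerance accounts for part of the 20% dropout. The protocol gives no reasons for dropout.
- That starting SAE collection at authorization is an error because treatment may begin up to 5 days earlier. It is a stated rule, consistent with authorization being required before entry.
- That the last-dose date will be unknown. Visits 4 and 5 and the treatment-duration groups cannot be worked without it, so at most a line is missing from the visit lists.

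**Conclusion.** The contradiction holds. The protocol promises a tabulation of adverse events leading to discontinuation, while every named collection step is limited to SAEs and none records why treatment stopped. As written, non-serious events that led to stopping would not be captured systematically and the count would be understated. The 6 to 16 patients out of 310 rest on an assumed 2% to 5% rate with no capture by other routes. They show scale and are not an estimate.

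The matter is moderate. It affects one supporting safety output. The primary endpoint, its confidence interval and the sample size do not depend on it. The end of SAE collection for patients treated past day 60 is a secondary inconsistency.

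**What to change.** Choose one of two routes.
1. Add to Table 2, Section 7.5.2 and the case report form, at Visits 2 and 3/Early Termination, the date of and reason for stopping. If the reason is an adverse event, serious or not, also record its term, severity and relationship. Extend Section 8.4 to cover these events.
2. Otherwise, restrict the Section 11.0 table to SAEs, including SAEs leading to discontinuation, and state in the protocol and report that non-serious events were not solicited.

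Route 1 costs one form item, amendment wording and a little site entry at visits that already take place. Route 2 costs wording only, but gives up the information.

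Separately, reconcile footnote 4 with footnote 9, Section 7.5 and Section 8.4, so that patients continuing past day 60 have one stated end to SAE collection. This needs wording, plus whatever contact the reconciled text requires.

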### **Sample size considerations**

Based on evaluation of literature data that was published by Gananca et al. in *Acta Oto-Laryngologica*, 2009 [17], proportion of patients with Meniere's Disease achieved control of vertigo (clinical conditions levels 4 and 3) after 12 weeks of treatment with betahistine dihydrochloride tablets constituted 88%. Benecke et al. [18] found that overall efficacy of betahistine in routine clinical practice over 3 months therapy was excellent by 36.6% of 1753 patients with recorded data (n = 641) and good by 49.6% of patients (n = 870), total 86.2 %. The investigators' impression of the treatment was excellent for 38.6% of patients (n = 675 of 1747) and good for 50.5% of patients (n = 883), total 89.1%.

For this program, it is assumed that at least 80% of the total study sample will achieve clinical response after 60 days of therapy with betahistine dihydrochloride tablets. When the sample size without a consideration of dropout is 246, a normal approximation two-sided 95% confidence interval for a single proportion using normal distribution will extend 5.0% (i.e. half width of the 95% confidence interval) from the observed proportion for an expected proportion of 80% [19; 20]. Considering an approximate dropout rate about 20%, total study population (received at least one dose of betahistine dihydrochloride (Betaseron®) tablets and have at least one post-baseline assessment) will constitute 308 patients.

Overall, the best consideration for total number of enrolled patients with vestibular vertigo in the program has to amount 310.

## **12.0 Final Report and Publications**

At the end of the program, a program report will be written in collaboration with the principal investigator(s) (Study Report will be issued within 10 months of Last Patient

[figure not shown]

Last Visit). This report will contain a description of the objectives of the PMOS, the methodology of the program and its results and conclusions. The completed case report forms and the program report must be treated as the confidential property of Abbott Laboratories and may not be released to unauthorized people in any form (publications or presentations) without express written approval from Abbott Laboratories. The results of this PMOS may be published by Abbott Laboratories or by any one of the participating investigators after written approval of Abbott Laboratories.

## 14.0 Appendix: Protocol Amendment 1: List of Changes

**Specific Changes** Amendment 1, dated 10 December 2012

### 1.1 Protocol Amendment 1: Summary of Changes

Section was added to describe changes under Amendment 1.

### Section 7.5 Program Conduct

**Figure 1: Overall Investigational Plan of Study previously read:**

**Figure 2: Overall Investigational Plan of Study**

[figure not shown]

[figure not shown]

Has been changed to read:

**Figure 2: Overall Investigational Plan of Study**

[figure not shown]

*Reason for changes:* figure clarification to be in line with the program conduct and figure number according to the correct appearance in the text.

[figure not shown]

**Table 1** Program Activities previously read:

| Weeks of Treatment                                                                                                                               |                        | Observational treatment period                                        |                                                                                   | Evaluation of the course of vestibular vertigo in follow-up period |                                                           |
|--------------------------------------------------------------------------------------------------------------------------------------------------|------------------------|-----------------------------------------------------------------------------------|-----------------------------------------------------------------------------------|--------------------------------------------------------------------|-----------------------------------------------------------|
|                                                                                                                                                  | Visit 1                | Visit 2                                                                           | Visit 3                                                                           | Visit 4                                                            | Visit 5                                                   |
|                                                                                                                                                  |                        | Expected up to 30 th day from the first dose of Betaserc®  | Expected up to 60 th day from the first dose of Betaserc®  | 30 th (±7) day from the last dose of Betaserc®          | 60 th (±7) day from the last dose of Betaserc® |
|                                                                                                                                                  | Screening/
Baseline |                                                                                   | End of observational treatment period  /Early termination           |                                                                    | End of follow-up period                                   |
| Patient Authorization (Consent) for Use/Disclosure of Data                                                                                       | X                      |                                                                                   |                                                                                   |                                                                    |                                                           |
| Inclusion / exclusion criteria                                                                                                                   | X                      |                                                                                   |                                                                                   |                                                                    |                                                           |
| Register date of start of betahistine dihydrochloride (Betaserc®) treatment                                                                      | X                      |                                                                                   |                                                                                   |                                                                    |                                                           |
| Demographics                                                                                                                         | X                      |                                                                                   |                                                                                   |                                                                    |                                                           |
| Medical history                                                                                                                                  | X                      |                                                                                   |                                                                                   |                                                                    |                                                           |
| Concomitant medication                                                                                                                           | X                      | X                                                                                 | X                                                                                 | X                                                                  | X                                                         |
| Physical Exam (including vitals  )                                                                                                   | X                      |                                                                                   |                                                                                   |                                                                    |                                                           |
| Specific underlying ICD-10 diagnosis account for Vestibular Vertigo                                                                              | X                      |                                                                                   |                                                                                   |                                                                    |                                                           |
| Number of monthly vertigo attacks                                                                                                                | X                      | X                                                                                 | X                                                                                 | X                                                                  | X                                                         |
| Scale for Vestibular Vertigo Severity Level and Clinical Response Evaluation                                                         | X                      | X                                                                                 | X                                                                                 |                                                                    |                                                           |
| Overall clinical response and clinical response as improvement of vestibular vertigo associated symptoms based on four-point scales  |                        | X                                                                                 | X                                                                                 |                                                                    |                                                           |
| SAE monitoring                                                                                                                       | X                      | X                                                                                 | X                                                                                 | X                                                                  |                                                           |

[figure not shown]

Has been changed to read:

